## Abstract

**Background:**

The CoAct (Cocreating Activity) study is investigating a novel lifestyle intervention, aimed at the working population, with daily activity monitoring and distance counselling via telephone and secure web messages. The main purpose of this study is to evaluate the effectiveness of lifestyle counselling on the level of physical activity in an occupational health setting. The purposes include also analysing the potential effects of changes in physical activity on productivity at work and sickness absence, and healthcare costs. This article describes the design of the study and the participant flow until and including randomization.

**Methods/Design:**

CoAct is a randomised controlled trial with two arms: a control group and intervention group with daily activity monitoring and distance counselling. The intervention focuses on lifestyle modification and takes 12 months. The study population consists of volunteers from 1100 eligible employees of a Finnish insurance company. The primary outcomes of this study are change in physical activity measured in MET minutes per week, work productivity and sickness absence, and healthcare utilisation. Secondary outcomes include various physiological measures. Cost-effectiveness analysis will also be performed. The outcomes will be measured by questionnaires at baseline, after 6, 12, and 24 months, and sickness absence will be obtained from the employer's registers.

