### Outcome measures, confounding- and mediating variables

Primary outcomes of the study are 1) physical activity level measured in MET hours per week, 2) health parameters (musculoskeletal and depressive symptoms) 3) work productivity and number of sickness absence days 4) healthcare utilisation. Effectiveness of the intervention is assessed by comparing the outcomes between the two treatment arms. Secondary outcomes are also listed in the Table 2.

**Table 2 T2:** Primary and Secondary outcome parameters

Outcome measure	Q, M, R	Baseline	6 months	12 months	24 months

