#### Sickness absence

Sickness absence days are analyzed from company's absenteeism and payroll records - each employee is required to inform the company when sick for one day to three days and required to get a certificate from occupational health when sick for longer than three days. Sickness absence data will also be collected for each employee from the year preceding the intervention in order to compare change over time.

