#### Healthcare utilization

As part of the first questionnaire the employees will be requested to complete a questionnaire concerning healthcare resource use during the past 6 months. This questionnaire includes questions of different healthcare resources used. This questionnaire is presented again at the 6 and 12 month time points.

Healthcare utilization data is also retrieved from occupational healthcare records. Data is retrieved based on social security number and study period data is compared to data from preceding year on individual level.

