### Sample size

The standard deviation for the IPAQ score in our population was estimated to be 1500 MET min-per-week. A difference of 400 MET min-per-week between treatment arms will be detectable with 85% power in two-tailed tests with the alpha of 0.05 for a sample of 253 employees in each group; the standardized effect size will be 0.25.

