### Statistical analyses

The effect of the intervention will be estimated on an individual level based on the intention-to-treat principle. For each primary and secondary outcome, a summary of results for each group, and the estimated effect size and its precision with confidence intervals will be presented. We will also assess potential effect modifying and mediating factors. The potential modifiers and mediators have been predefined and will all be measured at baseline. The potential effect modifiers are personal characteristics (age and gender), the result of the health risk appraisal (high/intermediate/low risk), baseline self-rated level of physical activity, baseline level of the ergometer test; job characteristics (specialist/manager), sick-leave related characteristics (sick leave days in the past year), and self-rated disability thoughts. The potential effect mediating factors are attendance to the PA intervention as intended, healthcare utilisation, and sick-leave related characteristics (sick leave days during the follow-up year).

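### The primary activity outcome is worded both as a change and as a level, and the stated 85% power is shown only for the level

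*Protocol article*

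**What the plan says.** The protocol article describes the primary physical activity outcome in two ways.

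- **As a change.** The abstract (Methods/Design) states that the "primary outcomes of this study are change in physical activity measured in MET minutes per week". The Discussion also speaks of changes in activity. It ties its reading of a negative result to having enough power to detect a meaningful change in activity level.
- **As a level.** The section on outcome measures lists "physical activity level measured in MET hours per week" and says that effectiveness is judged by comparing outcomes between the two arms. The abstract's statement of aim also refers to the level of activity. The Physical activity section computes a weekly score in MET-minutes, not a difference.

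The Sample size section says "The standard deviation for the IPAQ score in our population was estimated to be 1500 MET min-per-week". It continues "A difference of 400 MET min-per-week between treatment arms will be detectable with 85% power", using "two-tailed tests with the alpha of 0.05 for a sample of 253 employees in each group". It gives neither an SD of change nor a correlation between baseline and follow-up.

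The Statistical analyses section commits to intention to treat and to effect sizes with confidence intervals, and names no main-effect model. Baseline activity appears there in the list of potential effect modifiers ("baseline self-rated level of physical activity, baseline level of the ergometer test").

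For two other primary outcomes the text leans towards before-after comparison. Absence data are collected "from the year preceding the intervention in order to compare change over time". For occupational healthcare records, "study period data is compared to data from preceding year on individual level".

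**The concern.** A level at 12 months, an unadjusted change from baseline and a baseline-adjusted 12-month value all estimate the same between-arm difference under randomisation, but with different precision. A power statement therefore belongs to one of them. Here the SD is that of the score, so the calculation is for a level, while the abstract and Discussion speak of change. A reader cannot tell which analysis the 85% refers to, and the choice stays open until after the data are seen.

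The choice matters because an unadjusted change score carries the noise of the baseline measurement as well as that of the follow-up. If the two are only weakly correlated, subtracting baseline adds more variance than it removes. The Discussion intends to use a null result to direct occupational health resources elsewhere, on the ground that power was sufficient. That ground is weaker if the analysis performed is not the one that was powered.

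The units differ too: MET-minutes in the abstract, the scoring rule and the sample size, but MET-hours in the outcome list.

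**Working it through.** **Inputs from the Sample size section:** difference 400 MET-min/week, SD 1500 (of the score), two-sided alpha 0.05, power 85%, 253 per arm. **Assumed, because the article does not give them:** r, the correlation between baseline and 12 months, shown from 0.2 to 0.6; equal SDs at both times and in both arms; approximate normality.

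**1. The plan's own figure.** n per arm = 2 × (1.960 + 1.036)² × (1500/400)² = 2 × 8.98 × 14.06 ≈ 252.5, so 253. Power at 253 per arm is 85.1% by the normal approximation and 84.9% by the noncentral t. The stated figures reproduce for a comparison of scores with SD 1500.

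**2. SD under the other two analyses.**
- Unadjusted change: SD = 1500 × √(2(1 − r)). This exceeds 1500 when r < 0.5, equals it at r = 0.5 and is smaller when r > 0.5.
- 12-month value adjusted for baseline: residual SD = 1500 × √(1 − r²). This never exceeds 1500.

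Example at r = 0.4: change SD = 1500 × √1.2 = 1643; adjusted SD = 1500 × √0.84 = 1375.

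**3. Power at 253 per arm (noncentral t), and n per arm for 85% power (normal formula).**

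| r (assumed) | SD of change | Power, change | n, change | Adjusted SD | Power, adjusted | n, adjusted |
|---|---|---|---|---|---|---|
| 0.2 | 1897 | 65.8% | 405 | 1470 | 86.3% | 243 |
| 0.3 | 1775 | 71.6% | 354 | 1431 | 88.1% | 230 |
| 0.4 | 1643 | 78.0% | 304 | 1375 | 90.4% | 213 |
| 0.5 | 1500 | 84.9% | 253 | 1299 | 93.3% | 190 |
| 0.6 | 1342 | 91.7% | 203 | 1200 | 96.3% | 162 |

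**4. Why adjustment is not beaten.** The variance factors are 2(1 − r) for change and 1 − r² for adjustment. Their difference is (1 − r)², which is never negative. Their ratio is 2/(1 + r): 1.67 at r = 0.2 and 1.25 at r = 0.6. Against the level alone, adjustment multiplies the variance by 1 − r², which is at most 1. The only price is one degree of freedom, which is trivial at this sample size.

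**5. Units.** 400 MET-minutes is 400/60 = 6.7 MET-hours, and 1500 MET-minutes is 25 MET-hours. The ratio is the same, so the difference in units does not alter power. It is still an inconsistency in how the outcome is defined.

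No corresponding calculation is possible for absence or healthcare use, because the article gives no variance or correlation for them.

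**The case against.** The strongest reply is that the Methods section, not the abstract, defines the outcome. It defines a level compared between arms, for which 1500 is the right SD and 253 per arm is right. This stands: the sample-size arithmetic contains no error on this point.

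A second reply is that calling an outcome a change does not commit anyone to an unadjusted change-score test. Regressing change on arm and baseline gives the same arm effect and standard error as regressing the 12-month value on arm and baseline. The article names no model, and an analysis plan that is not shown may specify an adjusted one. This also stands. A reader might infer that the trial will analyse raw change and is therefore underpowered, but the article does not say so. Nor does listing baseline activity as a potential effect modifier rule it out as a covariate.

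Third, a shortfall needs r below 0.5. A reader might take the Discussion's remark that the questionnaire may be rather insensitive as evidence of a low r. It is not: an instrument that responds poorly to change could have a high correlation over time.

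The wording on absence and healthcare use is thinner evidence. It describes a comparison with the preceding year without naming a model, and the outcome section says that arms are compared.

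None of this reconciles the two definitions or shows that the 85% holds for change, which is how the abstract and Discussion describe the outcome.

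**Conclusion.** The point holds as an inconsistency in definition with a conditional consequence for power. The primary activity outcome is a change in MET-minutes in one place and a level in MET-hours in another, and the sample size supports the level. If unadjusted change were analysed, power at 253 per arm would run from about 66% at r = 0.2 to about 92% at r = 0.6, and would reach the stated 85% only from r = 0.5 upwards. Baseline adjustment would give about 86% to 96% over the same range and does not fall materially below 85% at any r.

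These figures rest on 1500 being the cross-sectional SD at both times and in both arms, on approximate normality, and on 253 per arm contributing data, so they are before any dropout. Because r is not given and no model is named, the documents do not show that the trial is underpowered or that a wrong analysis has been fixed. The proposed change deserves to be made because it removes the ambiguity and gains precision from data already in hand.

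**What to change.** - State one definition and one unit everywhere: MET-minutes per week at 12 months, the time point that the Background gives for the main purpose. Correct the abstract, the outcome list and the Discussion to match.
- Name the main analysis: linear regression of the 12-month value on arm, with baseline MET-minutes as covariate. Baseline activity can also remain a potential effect modifier in a separate interaction analysis.
- Say in the sample-size text that 1500 is the SD of the score and that baseline adjustment can only maintain or raise the stated power, before dropout. If the sponsor prefers unadjusted change, give the SD of change or the assumed correlation and recompute the sample size.
- For sickness absence and healthcare use from records, compare arms on study-period values with the preceding-year value as covariate, in place of individual before-after change.

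The cost is a few sentences of wording. Baseline activity, preceding-year absence and preceding-year healthcare use are all collected already, so no new measurement or recruitment is needed.

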**Discussion:**

No trials are yet available that have evaluated the effectiveness of daily physical activity monitoring and distance counselling in an occupational health setting over a 12 month period and no data on cost-effectiveness of such intervention are available.

**Trial Registration:**

ClinicalTrials.gov identifier: NCT00994565

## Background

Lack of physical activity (PA) and exercise are known determinants and risk factors for many diseases and disorders, e.g., overweight and obesity, cardiovascular diseases, adult-onset diabetes mellitus and some types of cancer [1,2]. Globally more than one billion adults are overweight (i.e., having a Body Mass Index (BMI) > 25 kg/m2) already and the numbers are still rising [3]. For those who are physically inactive, becoming active is important to alleviate overweight related health problems and to reduce chances of developing cardiovascular diseases and diabetes [4]. PA and exercise may also alleviate the symptoms of distress, depressive mood [5] and sleeping problems, alleviate back pain [6] and thus contribute to productivity at work.

The work setting provides an opportunity to introduce a large group of adults to a lifestyle modification programme. Such programmes in health care settings usually rely on lifestyle modification to change dietary intake and/or physical activity [7]. These strategies are known to produce weight loss [8,9]. However, only two previous randomised trial have been published on the effectiveness of PA interventions in the occupational setting, and the results have not been encouraging [10,11].

Typically lifestyle modification is provided by (individual or group) face-to-face counselling, requiring multiple visits to a treatment facility. This may be less appealing to working adults, who are often constrained by lack of time for such programmes. Behaviour counselling over the Internet (i.e., distance counselling) could be more feasible in the work setting. In other settings distance counselling has been applied to weight loss, dietary behaviours and physical activity. Phone counselling trials for weight loss, including trials primarily aimed at changes in diet and/or physical activity, showed mixed results [12-15]. The majority of phone counselling studies for physical activity and dietary behaviour found behavioural changes [16]. Few trials have investigated e-mail or internet counselling for weight control or lifestyle behaviours. Those that did, found positive effects on body weight, mixed effects on diet [17,18] and no effect on PA [17-19]. A recent randomized controlled trial concluded that distance counselling by phone or email is effective for reducing body weight in a group of overweight employees [20]. Studies that recruit participants from the work setting have, however, been rare [17,20].

The physical activity monitoring and distance counselling concept combines the use of a personal activity monitor with web-based tailored physical activity advice. Users can interactively plan and evaluate their own activity advice based on their actual PA scores and their PA preferences and goals. A recent randomised controlled trial [21] evaluated the effectiveness of such online physical activity advice based on a personal activity monitor and found that a 3-month intervention did not significantly affect PA levels and, furthermore, that a higher adherence to the program did not result in increased levels of PA. The study group comprised of a total of 102 physically inactive employees, 23 to 39 years old.

The main purpose of the present study is to evaluate the effectiveness on physical activity of a lifestyle programme with daily monitoring of activity and distance counselling compared to self help instruction, in a large cohort with a broad age spectrum of employees, at 12 months. Employees in the intervention group are given accelometers to wear daily and they will receive counselling via telephone and secure web messages. Subsequent purposes are to determine effects of the distance counselling on work productivity, sickness absence, healthcare utilisation and health outcomes when comparing to self help.

In the study we will be analyzing the lifestyle intervention's influence to health behaviour and if changes in health behaviour affect overall health. We are also interested in the lifestyle program's effects on productivity at work, including the potential effects on sickness absence. Furthermore, we will analyse potential effect modifying and mediating factors.

### Eligible population

Participants are employees of a large insurance company in Finland. Before the study is started all employees are invited to respond a health risk appraisal as part of their normal occupational healthcare (Figure 1). All employees will be approached through an invitational email and they will receive a screening questionnaire. These emails will be sent out all at once during mid August 2009. Out of a total of approximately 1100 employees 75% are expected to return the baseline questionnaire. The 75 percent response rate is expected because of an information campaign and since eligible participants can be individually reminded to participate.

**Figure 1 F1:**
[figure not shown]
**Occupational healthcare procedures taking place before the intervention study**.

A self-administered questionnaire is sent to all employees. The questionnaire [22] contains previously validated items about anthropometrics, sleep disturbances, work-related stress and fatigue, depression, pain, disability due to musculoskeletal problems and a prediction of future work ability (Table 1).

**Table 1 T1:** Items on the questionnaire and cut-off criteria for health problem

Topic	Questions	Criteria
Obesity	Height and weight, calculation of body mass index (BMI)	BMI ≥ 30
Alcohol consumption	Frequency and dosage. Modified from [36]	Alcohol/women: > 239 ml/abs alcohol/week: Alcohol/men: >349 ml/abs alcohol/week
Diabetes risk	Sum score of diabetes risk factors, scale 0-21; modification of DEHKO score [37]	Sum score ≥ 11
Pain	Frequency and intensity	At least "moderate" pain that "affects working ability" at minimum three times a week
Impairment due to musculoskeletal problems at work	Numerical rating scale (0-10) [38]	Impairment at work > 5
Depressive symptoms	Depression score DEPS, scale 0-30 [39]	DEPS ≥ 11
Stress and fatigue	Work related stress and fatigue [38,40]	"Very much" feeling of stress or fatigue because of work
Sleep disturbances	Modification of the Basic Nordic Sleep Questionnaire [41]	Problems in falling asleep or night awakenings AND daytime tiredness daily or almost daily
Daytime sleepiness	Epworth Sleepiness Scale, 0-24 [42]	ESS Score ≥ 11
Future working ability	Self-rated ability to continue working in the present job due to health problems after two years [43]	Uncertain of own ability ("Uncertain"), or quite sure ("Not able") not being able

The responses are interpreted on the basis of priori defined cut-off limits. Subjects who will report problems with future working ability, pain, impairment due to musculoskeletal problems, insomnia or insufficient sleep, frequent stress or fatigue, or have a high depression score, obesity, excess use of alcohol, or a high score in diabetes risk will be rated as having health problems (Table 1).

Based on self-reported health problems the employees are assigned to three groups: low-risk, intermediate and high-risk group. "High-risk" group is directed to a visit with occupational health. Employees receive advice or treatment and necessary follow up for their respective health problems. Targeted interventions at occupational health care for the "high risk" group have been shown to be effective in controlling sickness absence [23] and cost effective use of healthcare resources [24].

After the authorization of occupational physician the employee is directed to physical testing. "Low risk" and "intermediate risk" groups are scheduled for physical testing directly after receiving responses from the health risk appraisal. With the individual results employees are invited to schedule a time for physical testing through a web link. Most of the physical tests are done at the worksite during normal office hours. The physical test is done for voluntary participants as part of normal occupational healthcare.

### Physical testing

A background questionnaire concerning medical history and medication is filled in before physical testing. Employees can be excluded before or during the physical testing for multiple medical reasons: pregnancy, diagnosis or treatment of cancer, any disorder that makes physical activity impossible. Complete list of exclusion criteria is listed in Appendix 1. The test is started by measuring one's height, weight, waist circumference, body fat percentage and blood pressure. All measures are taken with previously validated measures and are described in more detail later. Aerobic fitness is measured by means of the indirect bicycle ergometer test (Aino Fitware). The test gives a prediction of the maximal oxygen uptake (VO2 max) during maximal exertion. The employee is asked not to eat, drink or smoke for 2 hours before this test. During the bicycle ergometer test the subject must report his/her subjective rate of exertion at the end of each stage using a scale of 6 to 20 [25]. The test is terminated when the pedalling rate drops under 60 rounds per minute. The estimated VO2 max is calculated with software analysis program (Aino Fitware). The AA Fitware test uses common validated procedures and measures from previous studies [26].

## Methods/Design

Once employees have completed the physical testing they will receive an invitation to participate in the randomised controlled trial. They will be handed an information leaflet in which the study protocol and the intervention options are clearly described. Employees can freely ask further about the study without any engagement. All employees willing to participate will individually sign an informed consent form that also allows for their personal data from the other data registers (health risk appraisal; physical testing; occupational healthcare utilisation; sickness absence records) to be collected to the research database and be used for the purposes of this study. The study received approval from the ethics review board (Helsinki University Hospital; Coordinating Ethics Committee) in August 2009.

CoAct (Coproducing Activity) is a randomized controlled trial with a two-year follow up. Randomization takes place at an individual level to two groups: to a control group and to an intervention group that receives a lifestyle intervention focusing on physical activity. The recruitment and data collection for this study will be started in August 2009. Data collection will continue until October 2011.

